## Abstract

**Background:**

Despite evidence that physical activity improves the health and well-being of prostate cancer survivors, many men do not engage in sufficient levels of activity. The primary aim of this study (ENGAGE) is to determine the efficacy of a referral and physical activity program among survivors of prostate cancer, in terms of increasing participation in physical activity. Secondary aims are to determine the effects of the physical activity program on psychological well-being, quality of life and objective physical functioning. The influence of individual and environmental mediators on participation in physical activity will also be determined.

**Methods/Design:**

This study is a cluster randomised controlled trial. Clinicians of prostate cancer survivors will be randomised into either the intervention or control condition. Clinicians in the intervention condition will refer eligible patients (n = 110) to participate in an exercise program, comprising 12 weeks of supervised exercise sessions and unsupervised physical activity. Clinicians allocated to the control condition will provide usual care to eligible patients (n = 110), which does not involve the recommendation of the physical activity program. Participants will be assessed at baseline, 12 weeks, 6 months, and 12 months on physical activity, quality of life, anxiety, depression, self-efficacy, outcome expectations, goals, and socio-structural factors.

**Discussion:**

The findings of this study have implications for clinicians and patients with different cancer types or other chronic health conditions. It will contribute to our understanding on the potential impact of clinicians promoting physical activity to patients and the long term health benefits of participating in physical activity programs.

**Trial registration:**

Australia and New Zealand Clinical Trials Register (ANZCTR): ACTRN12610000609055

Deakin University Human Research Ethics Approval 2011-085

## Background

Worldwide, prostate cancer is the second most common cancer in men. In 2008, 899,120 cases of prostate cancer were recorded, which represents 13.6 per cent of all new cancer cases in men. In the same year, 258,133 deaths were attributable to prostate cancer. It is predicted that the number of cases will almost double (1.7 million) by 2030 [1].

Prostate cancer is the most commonly diagnosed cancer in Australia and has the third highest mortality rate after lung and bowel cancers [2]. In 2007, 19,403 new cases of prostate cancer were diagnosed and there were 2,938 deaths. The rate of prostate cancer increases rapidly from the age of 45 years [2]. Improvements in five-year survival rates have been observed for prostate cancer, from 57% to 85% [3].

With improved survival rates, cancer survivors can derive substantial functional, physical, and psychological benefits from physical activity [4]. In men with prostate cancer, systematic review evidence suggests that physical activity has the potential to enhance health-related quality of life, muscular fitness, and physical functioning, as well as reduce fatigue [5]. Although these findings are promising, additional studies (especially randomised controlled trials in cancer types other than breast cancer) need to be conducted to substantiate the work in this area [4].

For prostate cancer survivors who have been treated with androgen deprivation therapy (ADT), there may be additional reasons to undertake physical activity. Previous research has shown that after 36 weeks of ADT prostate cancer patients decreased whole body lean mass by 2.4%, bone mineral content and density of 2.4%, serum testosterone of 93.3%, PSA levels of 98.2%, and haemoglobin levels of 8.8%, as well as increases in fat mass of 13.8% [6]. Assisting men who are receiving ADT to become physically active is, therefore, necessary to reduce the risk of obesity, osteoporosis and sarcopenia.

Many men reduce their involvement in physical activity following a diagnosis of prostate cancer [7]. Although evidence is mounting on the benefits of regular physical activity for prostate cancer survivors, the prevalence of physical activity among this group is modest and varies widely between studies [5]. To improve the uptake of physical activity among prostate cancer survivors, strategies need to be developed and tested for their effectiveness.

Research has highlighted gaps in information provision regarding the type and amount of physical activity that prostate cancer survivors should undertake [8]. A key challenge is to make such information accessible to all prostate cancer survivors. One way in which this information may be conveyed is via clinicians with referrals to accredited exercise physiologists. However, research has shown that most prostate cancer survivors do not recall receiving information from clinicians about integrating physical activity into their lives [8]. Patients have reported clinicians are the most important conveyors of information [9] and a prescription or referral to an exercise physiologist may be effective in promoting physical activity among patients.

Evidence on the efficacy of prescriptions of physical activity in general practice (GP) has been mixed [10-13]. In general, GP prescriptions of physical activity have led to a moderate increase in physical activity and fitness levels for 6 to 12 months [14]. There have been few studies, however, on the efficacy of physical activity prescriptions among people with specific chronic health conditions and where physical activity prescriptions are supplemented with other interventions, such as brief counselling [11]. Findings from this limited research have yielded less than optimal results. Overall however, the findings of previous studies are sufficiently strong to warrant further work in this area. The experience of cancer may mean that survivors more readily comply with the advice of their clinicians, which would result in higher levels of physical activity from an intervention that utilises clinician referral to an exercise physiologist in this population.

Accredited exercise physiologists are specialists who can provide prostate cancer survivors with expert advice on how to increase their physical activity levels safely. Since 2006 exercise physiologists accredited by Exercise and Sport Science Australia (ESSA) have been part of Australia's universal healthcare system (Medicare). Medicare provides access to free or subsidised treatment from medical practitioners, such as accredited exercise physiologists. Given their place in the health system, accredited exercise physiologists are well positioned to make an important contribution to increasing the health of prostate cancer survivors.

A criticism of previous randomised controlled trials that have examined physical activity in cancer survivor populations is that they do not incorporate a theoretical framework. Theoretical frameworks are necessary to guide the development and evaluation of interventions so that the mechanisms that change behaviour can be understood and replicated in future interventions [15]. There are compelling reasons for using social cognitive theory [16] to underpin a physical activity intervention for prostate cancer survivors. First, recent research conducted with (a) participants of similar ages to prostate cancer survivors who are likely to participate in this planned study [17], and (b) cancer patients [18] have shown that social cognitive theory constructs explain substantial amounts of variance in physical activity. For example, in a study of middle-aged and young-old adults, social cognitive theory constructs explained 71% of the variance in physical activity [17]. Second, social cognitive theory constructs are not only predictive of health behaviours, but provide avenues for modifying them [16,19].

The main determinants of health behaviour in social cognitive theory are self-efficacy, outcome expectations, goals, and socio-structural factors [19,20]. Self-efficacy is central to this conceptual model, and "refers to beliefs in one's capabilities to organise and execute the courses of action required to produce given attainments" (p. 3, [19]). Distinctions can be drawn between various types of self-efficacy, with task and self-regulatory (coping) self-efficacy common in the exercise and physical activity literature [21]. Task self-efficacy refers to the belief in one's ability to perform a given motor skill successfully (e.g., walking briskly for 30 minutes), whereas self-regulatory self-efficacy refers to one's ability to perform the skill under conditions that may be challenging to successful performance (e.g., inclement weather, tiredness).

Outcome expectations refer to the expected effects of one's behaviour [19]. These effects may be physical (beneficial or detrimental), social (favourable or adverse), or self-evaluative (positive or negative). Goals provide guidance to, and incentives for, behaviour. In social cognitive theory, goals are classified as being either proximal or distal [19]. Proximal goals are essentially equivalent to intentions and guide current behaviours, whereas distal goals orientate future behaviours. Socio-structural factors are facilitators and impediments to healthy behaviours. These factors may be personal or situational, or lie within the health system. Enhancing physical activity-related self-efficacy in prostate cancer survivors and assisting them to develop positive outcome expectations, set beneficial goals, and reduce perceived impediments may result in higher physical activity levels.

Our pilot work indicated that outcome expectations for prostate cancer survivors to perform physical activity reflected psychological and physical benefits that can be attained through participation, as well as from the context of activity, i.e. socio-structural factors, including attractive locations, opportunities for spending time alone, social interaction [8]. Conversely, impediments to participation included limited confidence following treatment, lack of time, co-morbidities, and age-related functional decline. Despite the benefits of physical activity, men in this study did not recall receiving advice from their clinicians about physical activity and few reported being referred to exercise professionals. Given these findings, interventions to increase physical activity in prostate cancer survivors that incorporate referrals from clinicians to exercise professionals and a well constructed theoretically tailored physical activity program may achieve positive outcomes.

### Study aims and hypotheses

The primary aim of the ENGAGE study is to compare the efficacy of a clinician referral and 12-week, supervised, exercise physiologist-led physical activity program compared to usual care (no referral to the physical activity program and typically minimal advice about physical activity) in improving the physical activity levels of prostate cancer survivors at three post-intervention time points:12 weeks, 6 months, 12 months. We hypothesise that participants in the intervention condition will be more physically active than participants in the control condition.

A secondary aim is to determine the effects of the clinician referral and physical activity program on the psychological well-being, quality of life and objective physical functioning of prostate cancer survivors. At the three post-intervention time points (12 weeks, 6 months, 12 months), we hypothesise that the clinician referral and physical activity program will improve participants' quality of life and decrease anxiety and depressive symptoms over and above changes on such measures that participants in the control condition may experience at post intervention. We will measure objective physical functioning at baseline and 12 weeks only, and hypothesise that participants in the intervention condition will improve their exercise capacity more than those in the control condition.

A further aim is to assess the impact of the intervention on main health determinants using the social cognitive theory and whether these determinants mediate behaviour change. We hypothesise that the intervention will have positive effects on self-efficacy, outcome expectations, goals, and socio-structural factors; and that self-efficacy will have a direct association with physical activity and an indirect association, mediated by outcome expectations, goals, and socio-structural factors.

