### Primary Outcome

Our primary outcome is the number of minutes of moderate-and strenuous physical activity per week as measured by an adapted version of the Leisure Time Exercise Questionnaire [32]. In this questionnaire, participants are asked to report the average weekly frequency and duration with which they engaged in strenuous, moderate, and light exercise over the past month. Consistent with a change made to the questionnaire in a study of colorectal cancer survivors [33], participants were asked to report the average duration of time they spent exercising at each intensity, in addition to the frequency. In addition, some of the physical activities were deleted from the instrument, because they were not common activities in Australia (e.g., horseshoes, snowmobiling). The validity and reliability of the Leisure Time Exercise Questionnaire compares favourably with other physical activity questionnaires [34].

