### Analysis

To address the primary aim of this study, we will conduct three main tests. To assess the impact of the intervention, we will perform an analysis of covariance (ANCOVA) on the post-intervention (12-week) physical activity levels of the participants in the two conditions, with their baseline scores as a covariate [53]. To determine the sustainability of the physical activity levels at 6 and 12 months, we will perform two ANCOVA on post-intervention (6 and 12 months, respectively) physical activity levels of the participants in the two conditions, with baseline scores as covariates.

To examine the data on the first of the secondary aims (determining the effect of the clinician referral and the physical activity program on psychological well-being, quality of life, and objective physical functioning) we will use the same analytical strategies as for the primary aim (ANCOVA with baseline scores as a covariates [53]). For this analysis, the dependent variables will be the subscales of the quality of life, anxiety, and depression measures, as well as the separate measures of objective physical functioning. The immediate effects of the intervention will be assessed using the 12-week data. The sustainability of the effects of the intervention on quality of life, anxiety, and depression will be assessed at 6 and 12 months.

To address the final aim, we will use path analyses to test for possible mediation of the intervention effect on level of physical activity based on the Baron and Kenny [54] approach. We will only test the components of SCT as possible mediators if they were affected by the intervention (i.e., group assignment) and associated with follow-up participation in physical activity. This approach requires that the outcome (i.e., participation in physical activity) be regressed on the proposed mediators (i.e. SCT components) and the intervention (i.e., group assignment coded as "0"= control and "1"= intervention). Mediation is present when the proposed mediator maintains a significant relationship with the outcome whereas group assignment does not. For the path analysis, we will adjust for the same variables as in the main analyses.

For all analyses, we will employ the intention-to-treat principle for all participants with available data at post intervention and follow-up.

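### The mediation rule for the third aim contains no path from self-efficacy to the other constructs, so the hypothesised indirect association goes untested

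*Protocol article*

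**What the plan says.** The third aim has two hypotheses, both in Study aims and hypotheses. The first is that "the intervention will have positive effects on self-efficacy, outcome expectations, goals, and socio-structural factors". The second is that "self-efficacy will have a direct association with physical activity and an indirect association, mediated by outcome expectations, goals, and socio-structural factors". The second describes a structure among the constructs themselves: self-efficacy comes first, three constructs lie downstream of it, and activity comes last, with a direct path from self-efficacy as well.

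The Analysis section takes up this aim on the Baron and Kenny approach:

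- Target: "we will use path analyses to test for possible mediation of the intervention effect on level of physical activity".
- Screen: "We will only test the components of SCT as possible mediators if they were affected by the intervention", with an association with activity at follow-up also required.
- Equation: "This approach requires that the outcome (i.e., participation in physical activity) be regressed on the proposed mediators (i.e. SCT components) and the intervention".
- Criterion: "Mediation is present when the proposed mediator maintains a significant relationship with the outcome whereas group assignment does not".

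**The concern.** The hypothesis concerns how self-efficacy reaches activity. The written analysis concerns how group assignment reaches activity, and it places all the social cognitive components side by side as candidate mediators of group. A trial that follows the text would produce no estimate of the path from self-efficacy through goals, expectations and socio-structural factors.

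A second consequence follows if the components share one equation. With its downstream constructs held fixed, the self-efficacy coefficient excludes everything that passes through them. The criterion nevertheless uses that coefficient to decide whether self-efficacy is a mediator.

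The Background treats self-efficacy as the core of the theory, and the Discussion presents the study of mechanisms as a main contribution. A finding that self-efficacy is not a mediator, when its influence runs largely through goals and expectations, could misdirect the design of later interventions.

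**Working it through.** **Hypothesis against analysis.**

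| Path in the hypotheses | Where the Analysis section examines it |
|---|---|
| group → each construct | screening step |
| self-efficacy → activity, direct | self-efficacy coefficient, if components are entered together |
| self-efficacy → expectations, goals, socio-structural factors | nowhere |
| those constructs → activity | their coefficients in the stated equation |

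An indirect effect is the product of the third and fourth rows. The third is missing, so the product cannot be formed.

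**Inputs for the size.** The article plans 220 participants and 10% attrition at 12 weeks: 220 × 0.9 = 198. It gives no path sizes, so every path size below is an assumption. Clustering is ignored and tests are two-sided at 0.05.

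**Check 1: one downstream construct.** Assume:

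- self-efficacy = 0.5 × group + e, with e of variance 1;
- goals = 0.6 × self-efficacy + 0.8e;
- activity = direct × self-efficacy + b × goals + 0.1 × group + 0.9e;
- total self-efficacy effect = direct + 0.6b = 0.4.

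Within group, self-efficacy and goals correlate 0.6, so the variance of self-efficacy given goals is 1 − 0.36 = 0.64. The standard error of the self-efficacy coefficient in the joint equation is about 0.9/√(198 × 0.64) = 0.080.

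| Share indirect | direct | b | z = direct/0.080 | Power, Φ(z − 1.96) | Simulated (4,000 trials) |
|---|---|---|---|---|---|
| 25% | 0.3 | 0.167 | 3.75 | 96% | 96% |
| 50% | 0.2 | 0.333 | 2.50 | 71% | 69% |
| 75% | 0.1 | 0.500 | 1.25 | 24% | 22% |

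The total effect is the same in every row. Only the route changes.

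**Check 2: three downstream constructs.** Assume group → self-efficacy 0.5, group → each construct 0.2, each construct → activity 0.25, no direct group effect on activity, and 1,000 trials per cell. The table gives the percentage of trials in which self-efficacy is significant in the joint equation.

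| Direct path | self-efficacy → construct 0.3 | 0.5 | 0.7 |
|---|---|---|---|
| 0.1 | 24 | 18 | 11 |
| 0.2 | 70 | 48 | 29 |
| 0.3 | 95 | 84 | 56 |
| 0.4 | 100 | 97 | 80 |

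**Does the criterion carry information on the chain?** Take a direct path of 0.3 and apply the criterion (self-efficacy significant, group not). With no chain at all, self-efficacy is called a mediator in 93% of trials. With a strong chain (0.7), it is called a mediator in 53%. The result moves against the hypothesis as the chain strengthens. A test that adds the missing equations and sums the indirect products detects the chain in 99–100% of trials when it exists and in 3% when it does not.

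**Screening.** In Check 1 the intervention moves goals only through self-efficacy, by 0.5 × 0.6 = 0.30 SD. The standard error of the group difference is √(2/99) = 0.142, so z = 2.11 and power is Φ(2.11 − 1.96) = 56%. A real link would fail the group screen in about 44% of trials. In Check 2 with a path of 0.5, the shift is 0.5 × 0.5 + 0.2 = 0.45 SD, z = 3.17, and the loss is about 11% per construct.

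**The case against.** Five points can be made on the other side.

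1. *The article names path analyses, which can hold the chain, and an article condenses a fuller plan.* This is fair as far as it goes, and full equations need not appear in an article. But the text is not silent. It states a specific equation and a specific decision rule as the way to address this aim, and neither answers the second hypothesis.

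2. *The hypothesis includes a direct association, and the joint coefficient estimates exactly that.* This stands. A reader might infer that the analysis generally dismisses self-efficacy when the hypothesis is true. The figures do not support that: with a direct path of 0.3–0.4 self-efficacy stays significant in 56–100% of trials in Check 2. A wholly indirect effect lies outside the hypothesis, so loss of significance there is no fault. A model that omits the downstream constructs estimates the total effect and is not a like-for-like comparison.

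3. *Joint entry is not certain.* The equation speaks of mediators in the plural, the criterion of one mediator. One-at-a-time entry is not excluded. It would remove the loss shown in the tables, but would still not test the chain.

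4. *The intervention is expected to shift all four constructs, so the screen should drop none.* If so, links are lost only through limited power. The 44% and 11% figures show that this loss can be material or modest, depending on the assumptions.

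5. *Timing.* For the primary outcome, "participants are asked to report the average weekly frequency and duration with which they engaged in strenuous, moderate, and light exercise over the past month", and the constructs are collected at the same visits. A reader might infer that the mediators would be measured after the behaviour they are meant to explain. The Analysis section does not say which visits are paired, and its wording is compatible with 12-week constructs and later activity. No timing error is shown.

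**Conclusion.** The concern holds in a limited form. The equation and criterion in the Analysis section do not test the indirect association of self-efficacy with activity. This follows from the text alone and does not depend on any simulation or on how the components are entered. The other parts of the third aim are addressed: the effect of the intervention on each construct, mediation of the group effect and, under joint entry, the direct self-efficacy association.

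Under joint entry, self-efficacy is also increasingly likely to be judged not a mediator as the indirect share of its effect grows: significant in about 96%, 69% and 22% of trials at 25%, 50% and 75% indirect. Those percentages rest on assumed path sizes, 198 evaluable men and no clustering, and they show direction and range only. The primary and secondary efficacy conclusions are unaffected.

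**What to change.** In the Analysis section, replace the single equation and significance rule with the path model that the hypotheses describe:

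- group to self-efficacy and to the other three constructs;
- self-efficacy to outcome expectations, goals and socio-structural factors;
- all four constructs and group to activity.

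Report the direct and indirect effects of self-efficacy, and the indirect effects of group, with confidence intervals. Do not decide mediation by whether one term is significant and another is not. Do not screen out components that form part of the chain.

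Keep the 12-week activity analysis, since it concerns the primary effect, and state which visits supply mediators and outcome. Optionally add a model with 12-week constructs and 6- and 12-month activity, so that the constructs precede the recall period.

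All constructs and visits are already planned. The cost is slightly more analysis work and a few sentences of text. The article states attrition only at 12 weeks, so the precision of the optional later models cannot be judged from it.
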